# Oral Misoprostol alone versus oral misoprostol followed by oxytocin for labour induction in women with hypertension in pregnancy (MOLI): protocol for a randomised controlled trial

**DOI:** 10.1186/s12884-021-04009-8

**Published:** 2021-07-29

**Keywords:** Pre-eclampsia, Induction of labour, Misoprostol, Oxytocin, Augmentation of labour, Randomized controlled trial, Study protocol

## Abstract

**Background:**

Every year approximately 30,000 women die from hypertensive disease in pregnancy. Magnesium sulphate and anti-hypertensives reduce morbidity, but delivery is the only cure. Low dose oral misoprostol, a prostaglandin E1 analogue, is a highly effective method for labour induction. Usually, once active labour has commenced, the misoprostol is replaced with an intravenous oxytocin infusion if ongoing stimulation is required. However, some studies have shown that oral misoprostol can be continued into active labour, a simpler and potentially more acceptable protocol for women. To date, these two protocols have never been directly compared.

**Methods:**

This pragmatic, open-label, randomised trial will compare a misoprostol alone labour induction protocol with the standard misoprostol plus oxytocin protocol in three Indian hospitals. The study will recruit 520 pregnant women being induced for hypertensive disease in pregnancy and requiring augmentation after membrane rupture. Participants will be randomised to receive either further oral misoprostol 25mcg every 2 h, or titrated intravenous oxytocin. The primary outcome will be caesarean birth. Secondary outcomes will assess the efficacy of the induction process, maternal and fetal/neonatal complications and patient acceptability. This protocol (version 1.04) adheres to the SPIRIT checklist. A cost-effectiveness analysis, situational analysis and formal qualitative assessment of women’s experience are also planned.

**Discussion:**

Avoiding oxytocin and continuing low dose misoprostol into active labour may have a number of benefits for both women and the health care system. Misoprostol is heat stable, oral medication and thus easy to store, transport and administer; qualities particularly desirable in low resource settings. An oral medication protocol requires less equipment (e.g. electronic infusion pumps) and may free up health care providers to assist with other aspects of the woman’s care. The simplicity of the protocol may also help to reduce human errors associated with the delivery of intravenous infusions. Finally, women may prefer to be mobile during labour and not restricted by an intravenous infusion. There is a need, therefore, to assess whether augmentation using oral misoprostol is superior clinically and economically to the standard protocol of intravenous oxytocin.

**Trial registration:**

Clinical Trials.gov, NCT03749902, registered on 21^st^ Nov 2018.

## Background

Hypertensive disease in pregnancy is a major cause of the 300,000 maternal deaths that occur every year [1]. In South Asia alone, hypertensive disease in pregnancy is responsible for 10,000 deaths annually [2]. Much of this burden could be prevented by timely and effective delivery—the only curative intervention in pre-eclampsia.

Misoprostol, a prostaglandin E1 analogue, given in low doses orally is a highly effective method for labour induction in low resource settings. Oral administration of 25 µg every 2 h received a strong recommendation by WHO in 2011 [3]. The Cochrane review of oral misoprostol found that in low doses oral misoprostol is at least as effective as the commonly used vaginal dinoprostone gel [4]. Misoprostol is also heat stable and less than 1% of the cost of dinoprostone gel. The Cochrane review concluded that “low-dose oral misoprostol probably has many benefits over other methods for labour induction.” and that “a starting dose of 25 μg may offer a good balance of efficacy and safety.” A recent network meta-analysis of all prostaglandins for labour induction supported these conclusions, finding that oral misoprostol solution (< 50mcg) was the safest in terms of risk of caesarean section [5].

Until recently, misoprostol was only available in 100 and 200mcg tablets (Cytotec®) which had to be either cut or dissolved in water to obtain the 25mcg doses [6–8]. However, low cost, high quality 25mcg misoprostol tablets have now become available, removing many of the logistical barriers to its use.

Standard practice for induction of labour is to use a prostaglandin (dinoprostone or misoprostol) for cervical ripening. When the amniotic membranes rupture and active labour has commenced (cervical dilation of more than 3-4 cm), the provider stops administering the prostaglandin and an intravenous infusion of oxytocin is started if uterine stimulation is still required [9]. Every 30 min the infusion is increased to stimulate uterine contractions sufficient to progress labour, but not so much as to cause hyperstimulation and consequent fetal hypoxia.

However, avoiding oxytocin and continuing low dose misoprostol into active labour may have a number of benefits for women and the health care system. Misoprostol is heat stable and an oral medication and thus easy to store, transport and administer; all particularly desirable in low resource settings. The ease of administration of an oral medication may help to reduce human errors associated with the delivery of intravenous infusions and require less equipment (e.g., electronic infusion pumps). Moreover, the simplicity of the protocol, which eliminates the need to actively titrate an oxytocin infusion against contractions, may free up health care providers to assist with other aspects of a woman’s care. Finally, women may prefer to be mobile during labour and not restricted by an intravenous infusion. There is a need, therefore, to compare the safety, efficacy and acceptability of the two augmentation protocols. The primary objective of this trial is to assess whether augmentation using oral misoprostol is superior clinically and economically to the standard protocol of intravenous oxytocin.

## Methods

### Trial design

We will undertake a multi-centre parallel, superiority, open-label randomised trial in three publicly funded hospitals in India: Government Medical College Nagpur, Daga Memorial Women’s Hospital and Mahatma Gandhi Institute of Medical Sciences.

### Participants and recruitment

Research staff will invite 1,000 potentially eligible women, due to undergo induction of labour with oral misoprostol, to provide advance written informed consent in case they become eligible. We estimate that 1,000 women undergoing induction will be required in order to obtain a sample size of 520 for the randomised trial, as not all patients will require additional drugs after artificial rupture of membranes. The randomised study will enrol 520 pregnant women, ≥ 18 years of age, with a live fetus, who require induction because of pre-eclampsia or hypertension and who have undergone cervical ripening with oral misoprostol alone but require an additional augmentation agent after membrane rupture. Those women unable to give consent, with previous caesarean births, those who undergo cervical ripening with agents other than misoprostol (e.g. Foley catheter, other prostaglandins), with multiple pregnancy, a history of allergy to misoprostol or adequate uterine activity will be ineligible.

After a decision has been made to induce labour, a patient information leaflet about the study will be given to the participant to read, consider and discuss with her partner and/or family. This leaflet will be available in local languages. Trained research staff will be available to answer any questions that women and their families have about the study. All will be assured that their participation is voluntary and that their decision to participate or not participate will not affect their clinical care. If the woman decides that she would like to participate in the study, research staff will ask the participant to sign a consent form, prior to any induction agent being administered. Participants will be assigned a participant ID number and all study data will be maintained separate from any relevant identifiers to participant names. She would then commence cervical ripening with oral misoprostol, as per routine practice. Following cervical ripening, the amniotic membranes will be ruptured artificially. If further uterine stimulation is required 30 min after artificial rupture of membranes, and the patient wishes to continue participating in the study, she would be randomised into either the misoprostol or oxytocin group.

### Randomization and masking

After the patient orally confirms her wish to participate in the trial, the research staff will open a sequentially numbered, sealed, opaque envelope containing the participant’s group. Gynuity Health Projects will generate the envelopes using a randomisation code based on a computerised pseudo-random number generator. Randomisation will be stratified by centre, with randomly determined block sizes of 4, 6 or 8. Neither the participating providers nor the participants will be blinded to the group assignment due to the complexity of titrating two separate uterotonics simultaneously.

### Procedures

The study flow is shown in Fig. 1. All women who consent to participate in the trial will undergo cervical ripening by the hospital staff who have received training in the study protocol. If the cervix is unfavourable, participants will receive oral misoprostol tablets (25 mcg) every 2 h for a maximum of 12 doses for cervical preparation. Once strong painful contractions (at least 3 in 10 min) have started, vaginal examination will be conducted. Contraction frequency will be assessed every 30 min and a vaginal examination done every 4 h to assess cervical dilation and Bishop score. Assessments may be conducted earlier if clinically indicated. The next dose of oral misoprostol will be omitted when moderate or strong contractions are occurring with a frequency of 3 in 10 min (i.e. 9 or more in the preceding 30 min). If the contractions become inadequate again, and the cervix is not yet 2 cm dilated then the misoprostol can be restarted at 25mcg every 2 h. If a clinical decision is made to use a mechanical method in addition to oral misoprostol for cervical preparation then the woman will no longer be eligible for the randomised trial. 'Artificial rupture of membranes’ (ARM) will be performed when the cervix is favourable (usually at 2 cm). No more cervical preparation doses of misoprostol will then be given. If spontaneous rupture of membranes occurs, then the cervical preparation doses of misoprostol will be stopped. If contractions are inadequate then further stimulation may be given as part of the randomised trial.

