### Outcomes

The primary outcome will be caesarean birth, a core outcome used in the Cochrane Collaboration induction of labour generic protocol [12], as the induction of labour core outcome set [13] had not been published at the time of protocol development. A tble of assessments is shown in Table 1. The need for caesarean birth combines the efficacy of the induction (important when induction is being conducted for hypertension in pregnancy) with the safety of the induction process for mother and fetus. It is a particularly important outcome as caesarean birth poses a serious risk to maternal health in the context of the setting and hypertensive disease. Secondary outcomes will include measures of efficacy of the induction process (randomisation to birth interval; vaginal births within 12 and 24 h of randomisation; duration of hospital stay); additional outcomes to allow meta-analysis (start of induction to birth interval; cervix unchanged at 12 and 24 h after the start of cervical preparation; vaginal births within 12 and 24 h after the start of cervical preparation); maternal complications (uterine tachysystole (defined as > 5 contractions in 10 min), uterine hypertonus (defined as a single contraction lasting over 2 min); and hyperstimulation syndrome (tachysystole/hypertonus with associated fetal heart rate abnormalities); uterine rupture; instrumental vaginal delivery; severe hypertension and HELLP Syndrome; maternal vomiting, diarrhoea or fever; antibiotic use; postpartum haemorrhage (> 1,000 ml, or any bleeding leading to systolic blood pressure less than 90 mmHg or diastolic blood pressure less than 60 mmHg or blood transfusion)) and serious maternal complications (intensive care unit admission; septicaemia; pulmonary oedema; cerebral haemorrhage or oedema; renal failure; eclampsia and maternal death). Maternal satisfaction will be assessed using a ‘Mother Generated Birth Satisfaction Index.’ Health economic data will also be collected to allow a full economic analysis of the intervention.

**Table 1 Tab1:** Schedule of enrolment, interventions and assessments

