### Sample size calculation

The sample size was estimated based on the primary outcome of caesarean birth assuming a rate of 31% caesarean birth for those receiving oxytocin for augmentation following cervical preparation with oral misoprostol. This is based on published data from a prior trial conducted in this population [14]. A total sample size of 520 women will provide (a) 90% power to detect a reduction in the caesarean rate from 31% to 18.5% (Relative Risk (RR) 0.6), or (b) 80% power to detect a reduction in the caesarean rate from 31 to 20% (RR 0.65) in those women who receive misoprostol (two sided α = 0.05). We estimate that we will need to approach and gain consent from 1,000 women requiring induction of labour for hypertension in order to find 520 who require augmentation after cervical preparation. When augmentation is indicated, consented women will be randomised either to a protocol of continued oral misoprostol (n = 260) or to the standard oxytocin infusion (n = 260).

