All regression models will be run unadjusted (i.e., with treatment group as the only independent/ predictor variable) and then re-run with adjustment for important potential confounder variables/ covariates. These include (but are not necessarily confined to) mother’s age, gestational age, cm dilatation before randomisation, receipt of magnesium sulphate in last 12 h, current anti-hypertensive use, time from hospital admission to randomisation of < 24 h, diastolic blood pressure at enrolment, proteinuria at enrolment, parity, and booked pregnancy. Other potential covariates will include variables found to differ by a clinically significant amount at baseline (post-randomisation) and measures identified as potentially affecting outcome during the study period. Subgroup analysis will be by site of delivery, parity and gestational age. Within the constraints of the O’Brien-Fleming stopping rules, overall statistical significance (across the interim and final analyses) will be set at the conventional 5% level for primary outcomes and p < 0.01 for secondary outcomes. A statistical analysis plan will be completed prior to prior to the first comparative monitoring report to be presented to the IDSMC.

The ISDMC will oversee the safety of participants in the trial. The terms of reference of the ISDMC will be developed separately, based on the principles developed by the DAMOCLES group. The ISDMC, who will have full access to the trial results analysed by allocation, will report directly to the TSC with recommendations about the conduct of the trial as well as whether to continue or stop the trial. The ISDMC will have the following independent voting members: [name] (London School of Hygiene and Tropical Medicine), [name] (Maulana Azad Medical College and Loknayak Hospital, New Delhi), [name] (Burnet Institute, Melbourne), and [name], (The University of Manchester).

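### The only named time covariate is a yes/no cut at 24 h from hospital admission; continuous time from first misoprostol dose to randomisation is available and would use the data slightly better

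*Protocol article*

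**What the plan says.** The Statistical analysis section runs each regression unadjusted and then adjusted. It names ten covariates. The one for time is "time from hospital admission to randomisation of < 24 h" and the one for the cervix is "cm dilatation before randomisation"; parity and gestational age are also named. Neither Bishop score nor length of ripening is. The list is expressly not exhaustive, and further covariates may enter if they differ at baseline or come to light during the study as affecting outcome.

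Under Procedures, ripening doses are given "every 2 h for a maximum of 12 doses for cervical preparation", with "a vaginal examination done every 4 h to assess cervical dilation and Bishop score". Under Outcomes, the secondary outcomes include the "start of induction to birth interval" and also the interval from randomisation to birth. Participants and recruitment restricts the randomised trial to women already ripened with oral misoprostol alone. Randomisation is stratified by centre only.

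**The concern.** The trial compares more misoprostol with oxytocin in women who have already been through a misoprostol course of varying length. How long that course took is a plausible predictor of caesarean birth under either policy. The named time covariate captures it poorly for two reasons:

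- **Origin.** The clock starts at admission. Nothing in the article ties admission to the first dose, so any wait before induction is mixed with the length of the induction itself.
- **Form.** A yes/no split treats all women on the same side of 24 h as alike, which discards information in any continuous predictor.

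At stake is some precision in the adjusted analysis, and adjustment for chance imbalance in how long induction has already taken, which stratification by centre does not control. The cut is written into the article, so this is a stated choice rather than a detail left to an unseen analysis plan.

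**Working it through.** **1. Is the better variable available?** Hours from start of induction to randomisation = (start of induction to birth) − (randomisation to birth). Both terms are listed secondary outcomes. Birth cancels, so the result depends only on two times before allocation. Eligibility requires prior misoprostol ripening, so it exists for every randomised woman.

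**2. The plan's own power.** Inputs from Sample size calculation: 31% on oxytocin, against 18.5% or 20% on misoprostol; 260 per arm; two-sided α = 0.05. Formula (pooled variance under the null, no continuity correction):

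power = Φ{[(p₁ − p₂)√n − 1.96√(2p̄(1 − p̄))] / √(p₁(1 − p₁) + p₂(1 − p₂))}

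- 31% v 20%: (0.11 × 16.12 − 1.96 × 0.616) / 0.611 = 0.925, giving 82.2% (stated: 80%).
- 31% v 18.5%: (0.125 × 16.12 − 1.96 × 0.610) / 0.604 = 1.357, giving 91.3% (stated: 90%).

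The design figures hold up. They assume no adjustment, so this point does not touch them.

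**3. What added explained variance buys.** The documents give no prognostic strength, so R² is an assumption. For a linear risk-difference model, effective N = 520/(1 − R²) and the standard error is multiplied by √(1 − R²).

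| Added R² (assumed) | Effective N | Fall in SE | Power, 31% v 20% |
|---|---|---|---|
| 0 | 520 | – | 82.2% |
| 1% | 525 | 0.5% | 82.6% |
| 2% | 531 | 1.0% | 83.0% |
| 5% | 547 | 2.5% | 84.1% |
| 10% | 578 | 5.1% | 86.0% |

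**4. What a binary cut loses.** For a normal covariate split with a share q below the cut c, the fraction of R² retained is φ(c)²/[q(1 − q)]: 0.64, 0.58, 0.49 and 0.34 for q = 50%, 70%, 80% and 90%. Power points lost (31% v 20%) when the same variable is cut:

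| R² of continuous time (assumed) | q = 50% | 70% | 80% | 90% |
|---|---|---|---|---|
| 2% | 0.3 | 0.3 | 0.4 | 0.5 |
| 5% | 0.7 | 0.8 | 1.0 | 1.2 |
| 10% | 1.4 | 1.6 | 1.9 | 2.5 |

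This takes time in isolation. Any overlap with covariates already listed reduces the loss.

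**5. Against an approximation to the planned model.** Simulation: 4,000 trials per scenario, N = 520, 31% v 20%, robust linear risk-difference model. Dilatation plus binary time is compared with dilatation plus Bishop score plus continuous time. Correlations and odds ratios per SD are assumed.

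| Dilatation–Bishop correlation | OR per SD, Bishop | OR per SD, ripening time | Binary time | Continuous time + Bishop | Difference (points) |
|---|---|---|---|---|---|
| 0.6 | 1.35 | 1.35 | 83.1% | 83.4% | +0.3 |
| 0.6 | 1.65 | 1.65 | 83.7% | 85.6% | +1.9 |
| 0.6 | 1.65 | 1.00 | 83.3% | 84.8% | +1.5 |
| 0.8 | 1.35 | 1.35 | 84.2% | 84.0% | −0.2 |
| 0.8 | 1.65 | 1.65 | 83.8% | 85.0% | +1.2 |
| 0.8 | 1.65 | 1.00 | 82.4% | 83.0% | +0.6 |

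Simulation error is about 0.6 points per estimate. Two limits pull in opposite directions. The difference credits the time and Bishop changes together, so it overstates the time change alone. The binary variable here is cut from ripening time itself, so the added loss from counting from admission is not modelled.

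**The case against.** **The list is open.** This is right: neither variable is excluded, and a reader who infers that the plan rules them out goes too far. But openness does not alter the cut that is written down. Ripening time would then enter as a later, discretionary choice in an open-label trial, where naming it now would pre-specify it.

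**The 24 h item is not presented as a stand-in for ripening.** Also right. A reader might infer a substitution, but the article states none, and admission time may be wanted for its own sake. That would be a reason to keep it as a continuous term.

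**The cut need not be extreme.** Since 12 × 2 h = 24 h, one might infer that nearly every woman falls below it. The text caps doses rather than hours, doses can be omitted and restarted, and no admission-to-first-dose lag is given. Suppose time = exponential lag + 2 h × doses + 0.5 h. A woman with 9 doses is under 24 h if her lag is below 5.5 h, with probability 1 − exp(−5.5/mean): 84%, 60% and 37% for mean lags of 3, 6 and 12 h. With a 12 h mean, 1 − exp(−21.5/12) = 83% of women with one dose are under 24 h, so the cut then separates the two groups quite well.

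**Larger gains rest on strong assumptions.** A slope of 0.10 to 0.20 in log-odds per dose, with dose count set alone against the indicator alone, makes the difference worth 6 to 43 women in 520. Those slopes imply odds ratios of exp(1.1) = 3.0 to exp(2.2) = 9.0 for 12 doses against 1, which nothing in the documents supports. The comparison also ignores dilatation, parity and gestational age, which are already listed.

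**Bishop score.** Dilatation is one of its components. Membranes are usually ruptured at about 2 cm, which narrows the spread, and the last score may pre-date rupture. The case for replacing dilatation with it is not made.

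**The model link is not stated.** N/(1 − R²) applies to a linear risk-difference model. Under a logit link, adjustment does not narrow the interval for the log odds ratio, so a narrower interval cannot be promised.

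**Conclusion.** The point holds as a minor improvement in efficiency. The named time covariate is dichotomised and counted from an event that need not be the start of induction, while a continuous, better-anchored value before allocation can be derived from data the trial already collects. The gain is about 0 to 2 power points against an adjusted model with dilatation and binary time. That rests on assumed prognostic strengths (odds ratios of 1.35 to 1.65 per SD where an effect is assumed), assumed correlations of 0.6 to 0.8 between dilatation and Bishop score, and a linear risk-difference model. The documents supply none of these values.

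They do not support the stronger conclusion that the plan throws away substantial precision. Nor is anything invalid: the primary comparison is first run unadjusted, and the sample size does not depend on the covariates.

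**What to change.** In the covariate list under Statistical analysis, replace the binary admission item with continuous hours from first misoprostol dose to randomisation, pre-specified. If time since admission is wanted for another reason, keep it as a separate continuous term. The last Bishop score before randomisation may be considered in addition to dilatation, not in place of it, with no claim about the gain.

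The cost is one change of wording and possibly one more model term. No additional women, examinations or data items are needed.
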